**Inclusion criteria**
Aged ≥60 yearsNational Institutes of Health Stroke Scale ≤15 [35]Acute ischemic strokeStroke onset ≤96 hoursHospital admission ≤48 hoursInformed consent by patient or legal guardian
**Exclusion criteria**
AphasiaReduced consciousness, defined as Glasgow Coma Scale ≤8 [38]Delirium onset before study enrollmentMagnetic resonance imaging contraindication such as pacemakers or metal implantsPreexisting conditions such as prior stroke, seizures, or traumatic head injury within the past 3 months, pre-existing neuropsychiatric disorders (eg, dementia, depression, and schizophrenia) or developmental delayHigh-grade paresis or plegia of the dominant hand

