## Introduction

Delirium is an acute clinical condition characterized by a wide range of symptoms affecting multiple domains. Patients with delirium often present with attention deficits, confusion, hallucinations, agitation, or disturbances in sleep-wake cycle. Typically, delirium occurs during critical illness, such as after surgery or stroke, with rapid onset and fluctuating symptoms [1]. Poststroke delirium (PSD) is one of the most common complications after stroke, with reported prevalence rates reaching up to 40% in older patients [1-3]. Both delirium in general and PSD in particular are associated with longer hospitalization, higher mortality, accelerated cognitive decline, and lower quality of life [1,4-11]. There is a broad consensus of a multifactorial origin [1,12,13], with predisposing factors such as dementia, age, comorbidities, and precipitating risk factors, including infection, stroke, or surgery [1,12,13]. The presence of multiple and fluctuating symptoms is diagnostically challenging, especially in patients with stroke with communication difficulties (eg, aphasia), and requires clinical expertise and standardized screening tools, such as the well-established ICDSC (Intensive Care Delirium Screening Checklist) [14,15]. Despite the high prevalence and the nondeclining mortality rate over the past decades [2,7], objective diagnostic tools and prognostic biomarkers (ie, fluid or proteomic biomarkers), as well as protective markers for long-term cognitive outcome, have not yet been implemented in clinical practice and remain the focus of ongoing studies [5,16-18].

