WM^d^ span within NAB Module Attention [47]	✓	✓	✓
TMT—Part B [46]	✓	✓	✓
Verbal memory			
MIS^e^ within MoCA^f^ [48]	✓	✓	✓
Language			
LIS^g^ within MoCA [48,49]	✓	✓	✓
Visuospatial construction			
VIS^h^ within MoCA [48,49]	✓	✓	✓
Orientation			
OIS^i^ within MoCA [48,49]	✓	✓	✓
Cognitive impairment			
MoCA [48]	✓	✓	✓
Questionnaires assessing cognitive functioning			
Self-rating CFQ^j^ [50]	✓		
Relative questionnaire: IQCODE^k^ [51]	✓		
Depression			
GDS^l^ [52]	✓	✓	✓
Quality of life			
SF^m^-12 [53]	✓		✓
Global disability			
(p)mRS^n^ [54]	✓		✓
Delirium screening			
ICDSC^o^ [55]	✓	✓	✓
Stroke symptoms			
NIHSS^p^ [35]	✓	✓	✓
Other variables			
Verbal intelligence test (MWT-B^q^ [56])	✓		
Demographics	✓		
Stroke location, medical interventions, comorbidities, etc	✓		

a S: session.

b TMT: trail making test.

c NAB: Neuropsychological Assessment Battery.

d WM: working memory.

e MIS: memory index scale.

f MoCA: Montreal Cognitive Assessment.

g LIS: language index scale.

h VIS: visuospatial index scale.

i OIS: orientation index scale.

j CFQ: cognitive failure questionnaire.

k IQCODE: Informant Questionnaire on Cognitive Decline in the Elderly.

l GDS: Geriatric Depression Scale.

m SF: Short Form health survey.

n (p)mRS: (pre)modified Rankin scale.

o ICDSC: Intensive Care Delirium Screening Checklist.

p NIHSS: National Institutes of Health Stroke Scale.

q MWT-B: German intelligence test *Mehrfach-Wortschatz-Intelligenztest*.

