In the second step, for the assessment of PSCI, a global and a domain-specific PSCI score will be defined in accordance with the guidelines of the International Society for Vascular Behavioral and Cognitive Disorders [68] and similarly to previous studies [39,69-72]. Further, the distinction between average cognitive functioning and mild, moderate, or severe cognitive impairment will be made according to the performance level on norm-referenced *z* scores, which is in line with the recommendations of multiple neuropsychological societies [73]. In detail, PSCI is a 5-level performance score. Performance level within 1 SD below or above the mean is defined as average cognitive functioning (PSCI=0). A range between 1 and 2 SDs below the mean (between third and 16th percentile) on at least 1 cognitive domain is defined as mild cognitive impairment (PSCI=1). A performance level 2 SDs below the mean (lower than the third percentile) in at least 2 domains is defined as moderate (PSCI=2), while a performance level 3 SDs below the mean (lower than the first percentile) in at least 2 cognitive domains or 2 SDs below the mean in most of the domains is defined as severe cognitive impairment (PSCI=3). Due to increased mortality in the PSD group, and to accommodate clinical realities as well as access feasibility of our study protocol, we use an intention-to-treat analysis for the primary end point. Therefore, we have added a level (PSCI=4), which reflects the death of a patient before the 3-month follow-up session. The following domains are defined: attention and information speed, executive functions, verbal memory, language, visuospatial construction, and orientation (Table 1). If a cognitive domain is represented by more than 1 test, the mean of the *z* scores will be used. We do not apply explicit weighting to individual test components when creating the composite scores for global and domain-specific poststroke cognitive function to ensure that each test within a domain contributes equally to the composite score, maintaining consistency with established neuropsychological standards. The primary endpoint will be a between-group comparison of the cognitive outcome, defined as global PSCI at a 3-month follow-up (S3). The groups will also be balanced for age and sex. Secondary outcome measures will be a between-group comparison of the domain-specific PSCI at a 3-month follow-up (S3).

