Further, multivariate linear regression models will be used to analyze multi-item prognostic or predictive tools for cognitive outcome (eg, global PSCI) at the follow-up measurement (S3) by multimodal parameters assessed during the acute phase poststroke (S1), such as NIHSS, acute treatment, and working memory performance during fMRI or fMRI connectivity measures. As some tests will be digitalized using a tablet and a digitizer pencil, new parameters representing search behavior, for example, time on surface and time in air [42,74], will be recorded and might help to differentiate between PSD and non-PSD groups or identify patients with stroke with a high delirium risk.

Missing data will be handled in the following manner. For missing data in a 2-test subdomain, we plan to use the *z* score of the other test within the same subdomain. For missing data in a single test subdomain, we plan to use a multiple imputation approach or maximum likelihood estimation.

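### The S3 comparison of PSCI between PSD and non-PSD patients is not stated to be adjusted for cognition before delirium, so impairment that predates the index stroke can appear as a PSD effect if it is more common in the PSD group

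*Protocol article*

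**What the plan says.** **Endpoint.** Under Statistical Analysis, Multicomponent Neuropsychological Assessment: "The primary endpoint will be a between-group comparison of the cognitive outcome, defined as global PSCI at a 3-month follow-up (S3". Levels 0 to 3 come from norm-referenced z scores in six domains, and level 4 is death before S3. The secondary outcome is the same comparison by domain. Neither is defined as a change from S1 or from the pre-stroke state.

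**Eligibility.** Textbox 1 lists among the excluded preexisting conditions "prior stroke, seizures, or traumatic head injury within the past 3 months, pre-existing neuropsychiatric disorders (eg, dementia, depression, and schizophrenia". It gives no cognitive cut-off for decline that has not been diagnosed.

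**Groups.** Study Design and General Procedures splits the cohort before S2 according to whether delirium has occurred. The Introduction describes delirium as multifactorial, "with predisposing factors such as dementia, age, comorbidities".

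**Baseline measures.** Table 1 schedules "Relative questionnaire: IQCODE" at S1 only, and the full test battery at S1, S2 and S3. S1 takes place after the index stroke and before delirium develops.

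**Controls.** "The groups will also be balanced for age and sex". The Discussion adds days post stroke as a covariate, to deal with variable assessment timing. A separate regression predicts S3 outcome from S1 parameters, "such as NIHSS, acute treatment, and working memory performance during fMRI or fMRI connectivity measures".

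**The concern.** The third objective is to tell PSD-related from stroke-related impairment. Impairment that was there before the index stroke is a third source. The endpoint cannot separate it, because it measures a level against norms. The groups are not randomised, and on the protocol's own account poor prior cognition and comorbidity predispose to delirium. Pre-stroke decline is therefore a candidate confounder of both the primary and the domain-specific comparison. None of the three stated controls addresses it, and the limitations in the Discussion do not mention it. The results are meant to guide larger multicentre studies, so a biased group difference would carry over into their design even if no test were significant here.

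**Working it through.** **1. Does a pre-stroke deficit count as PSCI?** Yes. The level depends only on the S3 z scores relative to the norm. A patient whose scores were already 1 SD low before the stroke keeps that 1 SD in the S3 score.

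**2. Can such patients enter?** Diagnosed dementia, depression and schizophrenia are excluded. Undiagnosed decline in people aged 60 or older is not screened by any stated threshold. For earlier strokes, the text "prior stroke, seizures, or traumatic head injury within the past 3 months" can be read in two ways:
- The limit covers all three conditions. A stroke more than 3 months old is then eligible.
- The limit covers head injury only. Any prior stroke is then excluded.

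**3. Is it controlled?** Age and sex are balanced and days post stroke is a covariate. The S1 regression is described as prediction, not as adjustment of the group comparison, and its examples do not include the IQCODE.

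**4. How large could the bias be?** The documents give no figure to reproduce and no inputs for this, so everything except the sample size and the scoring rule is assumed.

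From the article: 20 patients per group, six domains, and the PSCI level rule.

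Assumed:
- correlation of 0.5 between domains
- no deaths and no true PSD effect
- the severe rule's most-of-the-domains condition taken as at least 4 of 6
- a stroke effect of 0 or 0.5 SD, the same in both groups
- a pre-stroke deficit of 1 or 1.5 SD in all domains, in a share p1 of PSD and p0 of non-PSD patients
- a two-sided Mann-Whitney test at 0.05, with 4,000 repeats per scenario

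Spurious difference in mean PSCI level = (p1 − p0) × d, where d is the mean rise in level in a patient with the deficit. At 30% versus 10% the simulated differences run from 0.136 to 0.269. So d runs from 0.136 / 0.20 = 0.68 to 0.269 / 0.20 = 1.35 levels.

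| p1 vs p0 | Spurious mean difference (levels) | Rejection rate |
|---|---|---|
| 20% vs 20% | about 0 | 4-5% |
| 20% vs 10% | 0.07-0.14 | 6-7% |
| 30% vs 10% | 0.14-0.27 | 8-14% |
| 40% vs 10% | 0.21-0.41 | 14-24% |

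At 30% versus 10%, moderate-or-worse PSCI for a 1 SD deficit is 9.2% versus 5.0% without a stroke effect and 21.0% versus 13.3% with one. That is 0.042 × 20 = 0.8 and 0.077 × 20 = 1.5 extra patients in a group of 20.

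With a smaller deficit of 0.5 SD, and common mean z scores of −0.3 or −0.6, rejection is 4.7-5.2% at 20% versus 10%, 5.6-5.8% at 30% versus 10%, and 6.4-6.7% at 40% versus 15%. A rerun of these small-deficit scenarios gave the same picture, about 5-7%.

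The result turns on imbalance between the groups. With equal shares there is none to speak of.

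**The case against.** The strongest case against is that much here is silence in a condensed article, about an openly underpowered proof-of-concept study. Four stronger readings are tempting, and the documents support none of them.

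- *The IQCODE enters no analysis.* The list of S1 predictors is open, the IQCODE is an S1 measure, and questionnaires are to be analysed according to their manuals. What can be said is that no stated group comparison names it.
- *Strokes older than 3 months are eligible.* That is one reading of an ambiguous sentence. By itself it calls only for a clarification.
- *Pre-stroke decline will show up as a PSD effect.* This needs an imbalance among eligible patients. Diagnosed dementia, which the Introduction names as a predisposing factor, is excluded, and age is to be balanced. The Introduction makes an imbalance plausible but does not establish it.
- *S1 scores are no use as a baseline because they follow the stroke.* They cannot split pre-stroke from stroke deficit, but the contrast between PSD and non-PSD does not need that split. A score taken before delirium carries both sources and is a direct candidate for adjustment.

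It is also fair that no confirmatory claim rests on a nominal 5% test in this study. What stands after all this is that the article does commit itself to a level endpoint, to groups defined by delirium, and to a short set of controls. Those controls omit baseline cognition although the trial already measures it.

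**Conclusion.** The concern holds in this limited form. Impairment that predates the index stroke is scored as poststroke impairment. If it is more frequent in the PSD group it can pass for a PSD effect, and the stated controls do not prevent this. The size is unknown. Under the assumed inputs it runs from negligible (about 5-7% rejection for a small deficit or a small imbalance) to about 8-14% rejection and 0.14-0.27 PSCI levels at 30% versus 10% with a deficit of 1 to 1.5 SD. Wider imbalances give more, but nothing in the documents says how wide the imbalance is. The point deserves a change because it bears on the third objective and the remedy uses data already scheduled.

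**What to change.** 1. Prespecify that the S3 group comparison of PSCI, for example by an ordinal or rank-based model, is adjusted for baseline cognition already collected: the S1 IQCODE, the pre-delirium S1 cognitive score, or both. With 20 per group, keep to one or two such covariates.
2. Report the unadjusted and the adjusted result, and base any wording on PSD-related versus stroke-related impairment on the adjusted one.
3. State in Textbox 1 which conditions the 3-month limit covers.
4. Add pre-stroke cognition to the limitations in the Discussion.

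The cost is a few sentences of plan wording and one or two model terms; no new data are needed. The article places the start of analysis at the beginning of 2026, so the choice should be fixed before then. The downside is that some IQCODE values will be missing where no informant is available, which is a reason to name the S1 cognitive score as the alternative or companion covariate.

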### Study Population and Recruitment

This longitudinal proof-of-concept study aims to include a total of 40 patients with acute stroke, equally distributed in a PSD (n=20) and a non-PSD group (n=20). All the patients with acute stroke will be recruited from the wards of the Neurological Department of the University Hospital Tübingen.

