**Figure 1. F1:**
[figure not shown]
Overview of the RECOVER (Cognitive Recovery After Poststroke Delirium) study procedures. DSM-5: *Diagnostic and Statistical Manual of Mental Disorders, Fifth Edition*; DTI: diffusion tensor imaging sequence; FLAIR: fluid-attenuated inversion recovery sequence; ICDSC: Intensive Care Delirium Screening Checklist; MPRAGE: T1-weighted magnetization prepared rapid acquisition with gradient echoes sequence; MRI: magnetic resonance imaging; NIHSS: National Institutes of Health Stroke Scale; S1: session 1; S2: session 2; S3: session 3; T2*: T2-weighted echo planar imaging sequence; WM: working memory.

The three measurement points are as follows:

S1 during the acute phase poststroke (≤48 h after hospital admission; ≤96 h after stroke onset and before PSD development)S2 during the postacute phase poststroke (5‐14 d poststroke, depending on delirium recovery)S3 follow-up at 3 months poststroke (approximately 90 d poststroke)

Patients with stroke will be admitted to the Stroke Unit where a screening visit will be conducted, including a review of the inclusion and exclusion criteria. Following the review, written informed consent will be obtained from the patient or, if applicable, the legal guardian. Once consent has been obtained, the patient will be enrolled in the RECOVER study.

Each measurement (S1-S3) consists of a clinical examination, a multicomponent neuropsychological testing, and an MRI protocol. The MRI protocol is designed to acquire both structural (anatomical) data, as well as functional data (see the *Neuroimaging Protocol* section for more details). The clinical examination includes the National Institutes of Health Stroke Scale (NIHSS) [35] and will take approximately 15 minutes. The multicomponent neuropsychological assessment and the MRI scan (including positioning of patient) will each require 45‐60 minutes. A more detailed description is provided in the *Neuropsychological Assessment and Clinical Scores* section. S1 and S2 will be conducted as in-patient measurements, and the S3 3-month follow-up measurement will be conducted as an out-patient measurement.

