During the course of the longitudinal study, in particular before S2, the cohort of patients with stroke will be subdivided into 2 groups, those with PSD and those without (non-PSD). Delirium screening using the ICDSC [32] will be conducted throughout hospitalization to identify the onset and duration of delirium. To ensure timely detection of delirium onset and recovery, assessments will be performed every 8 hours. A diagnosis will be made according to the DSM-5 criteria by an independent neurologist, who will review the clinical course alongside the ICDSC data. Delirium recovery is defined as 3 consecutive negative ICDSC screenings.

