### Inclusion and Exclusion Criteria

This study includes patients with stroke with mild-to-moderate stroke symptoms (NIHSS ≤15; eg, [36,37]; Glasgow coma scale [GCS] >8). The prevalence of a PSD increases with age [20], reaching up to 40% among patients aged 60 years and older [1-3]. To ensure an equal distribution into the 2 study groups, only patients aged 60 years or older will be included in the RECOVER study. Textbox 1 gives an overview of all inclusion and exclusion criteria. When patients’ conditions or transfers preclude in-hospital assessment, follow-up visits at patients’ homes will be arranged.

Textbox 1.Inclusion and exclusion criteria for the study enrollment.

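### The planned 20/20 split of 40 patients does not follow from the design: at the protocol's own upper prevalence of 40% the expected split is 16 PSD and 24 non-PSD

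*Protocol article*

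**What the plan says.** Under Study Population and Recruitment, the protocol article aims to "include a total of 40 patients with acute stroke, equally distributed in a PSD (n=20) and a non-PSD group (n=20".

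Under Inclusion and Exclusion Criteria it names one means of reaching that split: "To ensure an equal distribution into the 2 study groups, only patients aged 60 years or older will be included in the RECOVER study". The preceding sentence supplies the rationale, a PSD prevalence "reaching up to 40% among patients aged 60 years and older". The Introduction gives the same ceiling: "with reported prevalence rates reaching up to 40% in older patients".

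Group membership is not fixed at entry. Under Study Design and General Procedures, session S1 takes place "≤96 h after stroke onset and before PSD development", and "in particular before S2, the cohort of patients with stroke will be subdivided into 2 groups, those with PSD and those without (non-PSD". Delirium that began before enrolment is an exclusion criterion. The article describes no quota, no group-specific stopping of enrolment and no over-enrolment.

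**The concern.** PSD status emerges only after enrolment and S1, so the number of PSD patients among 40 is a random outcome governed by incidence. A 1:1 split would need an incidence of 50%. The article quotes 40% as the top of the reported range, so an age limit justified by that figure cannot ensure equal groups.

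The eligibility criteria push the other way. They remove "pre-existing neuropsychiatric disorders (eg, dementia, depression, and schizophrenia", while the Introduction lists "predisposing factors such as dementia, age, comorbidities" among the contributors to delirium. Patients already delirious at enrolment, which may be up to 96 hours after onset, are removed from the PSD count directly. NIHSS above 15 and Glasgow Coma Scale of 8 or less are also excluded, while the Introduction reports more PSD after large anterior-circulation strokes. All of this bears on direction only; the article gives no size for the effect.

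At stake are the stated size of the PSD group and a clear statement of how the sample is formed. As written, a reader cannot tell whether 40 is the number enrolled or the size of a final cohort filled to 20 per group.

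**Working it through.** **Inputs from the article.** Total N = 40 with 20 PSD and 20 non-PSD (Study Population and Recruitment). Upper PSD prevalence p = 0.40 (Inclusion and Exclusion Criteria; Introduction). Groups known only after S1 (Study Design and General Procedures).

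**Assumptions.** Each enrolled patient develops PSD independently with the same probability p, and the quoted prevalence is used as that probability. This is generous to the plan, because prevalence includes cases that the criteria exclude. Rates of 30% and 25% are illustrations and do not come from the article.

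**Step 1: try to reproduce the stated figure.** Expected PSD count = N × p = 40 × 0.40 = 16, leaving 24 non-PSD. The stated 20 is not reproduced. It needs p = 20/40 = 0.50.

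**Step 2: how likely is the stated split?** With X ~ Binomial(40, p):

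| p | Expected PSD / non-PSD | P(X ≥ 20) | P(X = 20) |
|---|---|---|---|
| 0.40 (article's upper figure) | 16 / 24 | 0.130 | 0.055 |
| 0.30 (assumed) | 12 / 28 | 0.006 | 0.004 |
| 0.25 (assumed) | 10 / 30 | 0.0006 | 0.0004 |

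At p = 0.40 the standard deviation of X is √(40 × 0.40 × 0.60) = 3.1, and P(X > 16) = 0.43. Even at p = 0.50 exactly 20 would occur with probability only 0.125, so equality would not be ensured there either.

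**Step 3: enrolment needed for 20 PSD patients.** Mean enrolment = 20/p: 50 at 40%, 67 at 30% (20/0.30 = 66.7) and 80 at 25%. At 40%, an 80% chance of at least 20 PSD patients takes 57 enrolled. With 50 enrolled, about 30 would be non-PSD, which is 10 more than stated.

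**Step 4: precision.** Standard error of a difference in means, in SD units, = √(1/n₁ + 1/n₀):

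- 20/20: √(0.0500 + 0.0500) = 0.316
- 16/24: √(0.0625 + 0.0417) = 0.323, about 2% larger
- 12/28: √(0.0833 + 0.0357) = 0.345, about 9% larger
- 10/30: √(0.1000 + 0.0333) = 0.365, about 15% larger

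The primary endpoint is an ordinal impairment level from 0 to 4, with death as the top level, so these ratios describe the primary comparison only approximately.

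**The case against.** The strongest reply is that 40 patients at 20 per group is a recruitment aim and was never derived from prevalence. A quota is not ruled out: the article does not say that enrolment is consecutive, and the Statistical Analysis section says the groups will be balanced on age and sex, which may imply some selection. Recruitment mechanics are often left to the full protocol. The study also calls itself underpowered and makes no power claim that a 16/24 split would undermine.

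Much of this stands. The study's candour about power and the small loss at 16/24 mean that precision is not the main issue. A quota does not rescue the text, however. Filling 20 PSD places at 40% takes about 50 enrolled on average, against a stated total of 40, and the sentence about the age limit remains wrong under any recruitment scheme.

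A reader might infer three stronger things that the article does not support:

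- That 16 is a ceiling on PSD patients. It is an expected count at the highest quoted rate; more than 16 would occur with probability 0.43 at that rate.
- That the count will be 12, 10 or fewer. The exclusions support a lower rate in direction, but those figures rest on assumed rates.
- That non-PSD patients will be dropped after S1 to equalise the groups, which would make any delirium-risk work reflect an artificial 50% share. No passage describes this practice.

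**Conclusion.** The point holds as a mismatch between the stated sample and the design. On the article's own most favourable figure, enrolling 40 gives an expected 16/24 split, with a 13% chance of reaching 20 PSD patients and a 5.5% chance of the exact split stated. The age limit cannot ensure equal groups. These numbers rest on the 40% upper figure and on independent patients with a common risk; the true rate under these criteria is probably lower, by an unknown amount. The consequence is mainly an unsupported recruitment target and an undefined meaning of 40. The loss of precision is about 2% in standard error at 16/24 and reaches about 15% only if the rate is near an assumed 25%.

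**What to change.** Delete the statement that the age limit ensures equal groups. It can be replaced by saying that the limit raises the expected share of PSD patients. Then state one of two designs:

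- **No quota.** 40 patients enrolled, with an expected split of about 16/24 at the 40% upper figure and fewer PSD patients at lower rates (for example 12/28 at an assumed 30% and 10/30 at an assumed 25%, both labelled as assumptions), with the precision for that range.
- **Quota of 20 per group.** Total enrolment will exceed 40, about 50 on average at 40% and more at lower rates. State how surplus non-PSD patients are handled, preferably by keeping them in the analysis.

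The first option is a text change whose only cost is a less favourable stated PSD group size. The second costs additional recruitment: 15 patients had been included by May 2025, with recruitment planned to September 2025 according to the Results section.
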